# Efficacy of mistletoe extract as a complement to standard treatment in advanced pancreatic cancer: study protocol for a multicentre, parallel group, double-blind, randomised, placebo-controlled clinical trial (MISTRAL)

**DOI:** 10.1186/s13063-020-04581-y

**Published:** 2020-09-11

**Keywords:** Neoplasms, Pancreatic neoplasms, Mistletoe, Complementary therapies, Palliative care, Quality of life, Clinical trial, Randomised controlled trial

## Abstract

**Background:**

Most pancreatic cancer patients present with advanced stage at diagnosis with extremely short expected survival and few treatment options. A multimodal palliative approach is necessary for symptom relief and optimisation of health-related quality of life. In a recent open-label trial of mistletoe extract for advanced pancreatic cancer patients not eligible for chemotherapy, promising results on improved overall survival and better health-related quality of life were reported.

The objective of the present study is to assess the value of mistletoe extract as a complement to standard treatment (palliative chemotherapy or best supportive care) in advanced pancreatic cancer patients with regard to overall survival and health-related quality of life.

**Methods:**

The trial is prospective, randomised, double-blind, multicentre, parallel group and placebo-controlled. In total, 290 participants are randomly assigned to placebo or mistletoe extract given subcutaneously in increasing dosage from 0.01 to 20 mg three times per week for 9 months. Stratification is performed for site and palliative chemotherapy. Main inclusion criteria are advanced pancreatic cancer and Eastern Cooperative Oncology Group performance status 0 to 2; main exclusion criteria are life expectancy less than 4 weeks and neuroendocrine tumour of the pancreas. Two ancillary studies on sub-sets of participants are nested in the trial: a biomarker study collecting blood samples and a cross-sectional qualitative study with semi-structured face-to-face interviews.

**Discussion:**

To our knowledge, this is the first placebo-controlled randomised trial assessing the impact of mistletoe extract as a complement to standard treatment on overall survival and health-related quality of life in patients with advanced pancreatic cancer. The presented trial with its two nested ancillary studies exploring biomarkers and patient experiences is expected to give new insights into the treatment of advanced pancreatic cancer.

**Trial registration:**

EU Clinical Trial Register, EudraCT Number 2014-004552-64. Registered on 19 January 2016.

ClinicalTrials.gov NCT02948309. Registered on 28 October 2016.

## Administrative information

Note: the numbers in curly brackets in this protocol refer to SPIRIT checklist item numbers. The order of the items has been modified to group similar items (see http://www.equator-network.org/reporting-guidelines/spirit-2013-statement-defining-standard-protocol-items-for-clinical-trials/).

## Introduction

### Background and rationale {6a}

Pancreatic cancer is currently the fourth most common cause of cancer-related deaths worldwide and is estimated to climb to second place by 2030 [1]. Despite improved treatment strategies, the prognosis remains extremely poor. The combined impact of severe symptoms and comorbidities associated with the disease most often lead to a rapid deterioration of performance status and health-related quality of life (HRQoL). According to a systematic review on real-world data from Europe, the disease causes an almost complete loss of healthy life [2]. One-year survival for all stages is about 21% and 5-year survival about 9% [3]. The only option for cure is surgical resection, preferably followed by 6 months of postoperative combination chemotherapy [4, 5]. Unfortunately, 80–85% of the newly diagnosed patients present with locally advanced and/or metastatic disease which preclude this type of curative intent strategy. In addition, most of patients undergoing curative intent surgery will relapse in 2 to 3 years [6].

For patients with primary unresectable disease, or recurrent disease under the post-resection follow-up, survival time is usually short. In these groups, a multimodal palliative approach is necessary to relieve cancer-related symptoms such as nausea, loss of appetite and weight, cachexia, and fatigue, and to optimise the HRQoL. In patients with adequate Eastern Cooperative Oncology Group (ECOG) performance status 0 to 2 and acceptable organ functions, palliative chemotherapy may prolong life and reduce disease-related symptom burden. For reasonably ‘fit’ patients treated with chemotherapy combination regimens such as gemcitabine/nab-paclitaxel or FOLFIRINOX, overall survival is usually between 8 and 11 months [7–10]. For patients with lower performance status and comorbidity, best supportive care or palliative chemotherapy with milder regimens such as gemcitabine monotherapy remain the only therapeutic options. In these groups of patients, survival is usually limited to around 1–2 [9] and 6 months respectively, the latter which appears similar in randomised controlled trials and real-world populations [7–9, 11].

Palliative supportive care, both as in- and outpatient care, is publicly funded and available to all patients in Sweden regardless of socioeconomic status.

Mistletoe (*Viscum album* L.) extract (ME) is widely used in integrative cancer care treatments, particularly in Europe [12–14]. *Viscum album* L. is a hemiparasitic shrub, growing on different host trees. Several pharmacologically active compounds have been isolated, such as mistletoe lectins I, II and III [15], viscotoxins [16, 17], oligo- and polysaccharides [18, 19], lipophilic extracts [20], triterpenes [21, 22] and others [23, 24]. The most prominent properties of ME are their cytotoxic and growth-inhibiting effects, which have been demonstrated in a variety of human tumour cell lines, lymphocytes and fibroblasts in vitro [23, 24]. The cytotoxic effects are mainly due to the apoptosis-inducing mistletoe lectins, while the viscotoxins induce necrotic cell death [23–25]. ME are also recognised for their immune-modulating activity: activation of monocytes/macrophages, granulocytes, natural killer (NK) cells, NK cell-mediated tumour cell lysis, T cells (especially T helper cells), boost of T cell-mediated killing and induction of various cytokines [23, 24, 26, 27]. Further, components of ME also downregulate the expression of tumour genes, reduce motility and invasiveness of tumour cells [26] and show antiangiogenetic effects [28]. They also reduce chromosome damage and improve endogenous DNA repair mechanisms [23, 24, 29, 30]. In animals, ME display anti-tumour effects when administered either directly into the tumour or systemically [23, 24, 27, 31].

Clinical effectiveness of ME in cancer has been investigated in many studies with various designs and methodological quality—among these, more than 40 prospective randomised controlled trials [23, 31–39]. With regard to study quality and consistency of results, the best evidence exists for improvement of HRQoL and enhanced tolerability of cytoreductive therapies [32, 33, 35]. Regarding survival, a randomised controlled Serbian trial including 220 patients with advanced pancreatic cancer not eligible for palliative chemotherapy reported a median survival of 4.8 months among ME-treated patients compared with 2.7 months in the control group (HR = 0.49; 95% CI = 0.36–0.65; *p* < 0.0001). The survival benefit of ME was larger among patients with good prognostic features (6.6 vs. 3.2 months) than with poor prognostic features (3.4 months vs. 2.0 months) [36]. In addition, patients reported substantially better HRQoL and tended to gain weight when treated with ME compared to the control group [35]. Two phase I/II trials and some retrospective studies also reported favourable outcomes regarding safety and efficacy of ME in patients with pancreatic cancer [40–42]. Tumour remission under ME is rare but has been reported in some small studies and case reports, mostly applying high-dose ME directly at the tumour site [31, 43–46]. Ongoing trials investigate ME in bladder cancer (NCT02106572) and other advanced solid tumours (NCT03051477). ME are considered safe and well tolerated even among immunosuppressed patients. However, in rare cases, a generalised allergic reaction may occur [23, 24, 47, 48]. Unwanted and/or clinically significant interactions with ME and established chemotherapeutic drugs have not been observed [23, 40, 49–52].

### Objectives {7}

The overall objective of the present trial with two ancillary studies is to assess the value of ME as a complement to standard treatment in advanced pancreatic cancer.

The primary objective is to compare overall survival (OS) in patients with advanced pancreatic cancer randomised to either ME or placebo.

The secondary objectives are to compare health-related quality of life (HRQoL), body weight, corticosteroid use, adverse events (AE) and costs for supportive care and inpatient care.

Ancillary studies

Two ancillary studies aim to
Assess immunological effects and to explore potential prognostic and predictive biomarkers (biomarker study).Explore advanced pancreatic cancer patients’ experiences of every-day life (qualitative study)

### Trial design {8}

The study is designed as a phase III prospective, randomised, double-blind, multicentre, parallel group, placebo-controlled clinical trial. A total of 290 participants are randomly assigned to receive ME or placebo in a one-to-one ratio, stratified by site and palliative chemotherapy (eligible or not). Superiority testing will be used.

Ancillary studies

Two ancillary studies on sub-sets of participants are nested in the trial:
A biomarker study collecting blood samplesA cross-sectional qualitative study with semi-structured face-to-face interviews

## Methods: participants, interventions and outcomes

### Study setting {9}

The trial is an academic multicentre study and started with a limited number of study sites due to organisational reasons. Subsequently, additional study sites have been amended to reach target inclusion as fast as possible. Currently, nine qualified study sites in Sweden are participating: community hospitals in Västerås (Västmanlands Hospital), Jönköping (Ryhov County Hospital), Skövde and Lidköping (Skaraborg Hospital), Karlstad (Central Hospital Karlstad), Kalmar (Kalmar County Hospital) and the South General Hospital in Stockholm, as well as the University hospitals in Umeå (University Hospital of Umeå), Linköping (University Hospital of Linköping) and Stockholm (Karolinska University Hospital).

Ancillary studies
Current study sites collecting data for the biomarker study: South General Hospital in Stockholm, University Hospital of Linköping and Karolinska University HospitalStudy sites collecting data for the qualitative study: Västmanlands Hospital, Karolinska University Hospital, South General Hospital and University Hospital of Linköping

### Eligibility criteria {10}

#### Inclusion and exclusion criteria for participants

Patients eligible for inclusion in the trial and the two ancillary studies must meet all the following criteria:
Signed written informed consentAge ≥ 18 yearsInoperable locally advanced or metastatic pancreatic cancer or relapse of pancreatic cancerPrimary diagnosis: if histology is not clinically achievable, diagnosis is to be confirmed according to local practice sufficient for diagnosis and choice of therapy (such as CA19-9 and CT)Relapse: histology (not required) or diagnosis according to local practice such as clinical signs and/or imaging and/or CA19-9ECOG performance status 0–2Adequate negative pregnancy test and adequate contraception (where appropriate)

Exclusion criteria
Life expectancy less than 4 weeksPregnancy or breastfeedingNeuroendocrine tumours of the pancreasCurrent use of interferon, granulocyte-colony stimulating factor and thymus preparationsSymptomatic brain oedema due to brain metastasesKnown hypersensitivity to mistletoe-containing productsCurrent use of ME preparations in any formChronic granulomatous disease or active autoimmune disease or autoimmune disease with immunosuppressive treatmentMedical, psychiatric, cognitive or other conditions that may compromise the patient’s ability to understand the patient information, give informed consent, comply with the study protocol or complete the study (e.g. needle phobia)

#### Study site requirements

Centre selection is based on the presence of appropriate clinical and research infrastructure (research unit with study nurses) and principle investigators (oncologists) with Good Clinical Practice (GCP) qualifications.

Ancillary studies
The biomarker study is being conducted at some of the centres where biobanking and sample collection was organizationally possibleThe qualitative study is being conducted at four centres representing urban, rural and small-town environments for purposeful sampling

### Who will take informed consent? {26a}

It is each investigator’s responsibility to give adequate oral and written information on the study’s purpose and procedures, information on data protection procedures, possible advantages and disadvantages of participation, and option to withdraw from the study at any time and without any given reason. Written informed consent must be obtained for all participants prior to any trial-related procedures.

### Additional consent provisions for collection and use of participant data and biological specimens {26b}

For the ancillary studies, separate information sheets are provided, and written informed consent must be signed prior to
Any collection of blood samples in the biomarker study andPrior to face-to-face interviews in the qualitative study

## Interventions

### Explanation for the choice of comparators {6b}

Isotonic saline solution was chosen as a placebo to avoid any possible harm from injections and because it is the vehicle of used ME.

### Intervention description {11a}

The study intervention consists of subcutaneous injections with a herbal fermented aqueous extract of *Viscum album* L (Santalaceae; European mistletoe) grown on *Quercus* (Fagaceae; oak tree). The product used is Iscador® Qu, manufactured by Iscador AG, Switzerland. The product is registered as a herbal medicinal product for well-established use in Sweden. The drug substance is a fermented aqueous extract of fresh mistletoe (drug-to-finished extract ratio 1:5) mixed with water and sodium chloride to achieve an isotonic solution.

Composition of 1 mg ampoule:

**Table Tabb:** 

Product	Quantity of drug substance per 1 mg ampoule; extract 1:5	Corresponding amount of fresh mistletoe
Iscador® Qu 0.01 mg	0.05 mg	0.01 mg
Iscador® Qu 0.1 mg	0.5 mg	0.1 mg
Iscador® Qu 1 mg	5 mg	1 mg
Iscador® Qu 10 mg	50 mg	10 mg
Iscador® Qu 20 mg	100 mg	20 mg

Mistletoe species and host tree are identified visually by a botanist. Extracts are characterised by a chromatographic identity test and have a specified content of viscotoxins as marker substances. Retained samples of active ingredient and the study medication are kept at the manufacturer headquarters of Iscador AG, Switzerland.

Participants (or their next of kin) are instructed in injection technique (injection speed 20–30 s, injection site abdominal wall or, if not possible, proximal thigh). Treatment is given with one ampoule (1 ml) 3 days per week (Monday–Wednesday–Friday or Tuesday–Thursday–Saturday), preferably in the morning on chemotherapy-free days to minimise the risk of potentially confounding side effects of chemotherapy. The dose is gradually increased, starting with two 0.01 mg injections over four 0.1-mg, four 1.0-mg and four 10-mg injections, followed by the highest possible dose of 20 mg as the maintenance dose for the rest of the trial. Participants receive boxes with the study drug in 1-ml ampoules in different colour-coded concentrations.

### Criteria for discontinuing or modifying allocated interventions {11b}

Study drug application and dose increase may be modified as below for the following reasons:

#### Maintenance of dose

According to traditional clinical use, occurrence of local reactions (defined as redness < 5 cm, itching, warmth, swelling within hours after injection and ceasing within 48 h) leads to maintenance of the actual dose until no further local reaction has occurred for 1 week; then, outlined dose increase is continued.

#### Reduction of dose

The dose is reduced if a local *over*reaction (defined as local reaction with redness > 5 cm and/or remaining for > 48 h) or malaise or flu-like symptoms according to the Common Terminology Criteria for Adverse Events (CTCAE) [53] grade ≥ 2 or fever > 38 °C (not caused by infection or tumour) with clear time correlation to dose increase and treatment days are observed. Half (=0.5 ml) of the ampoule content of the symptom-causing dose will then be used for 2 weeks, and subsequently the former symptom-causing dose, followed by the planned dose increase are given. If the symptoms recur, participants stay at the lower dose. If fever occurs due to the trial intervention, antipyretics are dissuaded, except for analgesic purposes. If an activation of local chronic inflammatory processes is observed (a very rare side-effect of ME), dosage is decreased and adapted individually.

#### Temporal interruption of trial intervention

The study treatment will be temporarily interrupted in case of acute infectious disease with fever > 38 °C and/or clinical symptoms from a clinically relevant infection. Upon clinical recovery, treatment continues with the next lower dose and the dose is increased as planned.

#### Termination of trial intervention

Study treatment is terminated after 9 months from the baseline visit. Treatment may be terminated earlier due to the participant’s own decision to withdraw consent or in case of medical, psychiatric, cognitive or other conditions occurring that may endanger the patient’s ability to comply with study protocol or complete the trial. Other reasons for early treatment termination are serious adverse events with suspected causal relationship to the study drug (such as allergic reaction CTCAE Grade ≥ 2, anaphylaxis, erythema multiforme or other events which may cause severe or permanent harm), or major violation of study protocol. The treatment might also be stopped in the very late palliative stage, if a potentially life-extending effect is no longer considered desirable.

### Strategies to improve adherence to interventions {11c}

#### Drug account

At each visit, intervention dosage according to the protocol is prescribed and documented in the study-specific patient diary, where participants also keep a record of the administered injections. Participants are dispensed as much study drug as needed until the next scheduled visit, plus extra supplies to cover for potential dose modifications or change of visits for any reason. To evaluate adherence to treatment, participants return their completed diary at each follow-up visit and receive a new diary covering the time until next outlined visit (Fig. 1).

#### Education study sites, palliative home care teams

Study sites and related palliative home care teams are instructed on study procedures at start meetings and subsequently based on local needs during the trial. Annual national trial meetings for study personnel and investigators are held, and a periodical newsletter is sent for updates on the state of the study.

### Relevant concomitant care permitted or prohibited during the trial {11d}

Through the Swedish health care system, participants have access to palliative supportive care, either as in- or outpatient care, for symptom relief and psychological and social support.

Initiation or termination of or switch to a new line of palliative chemotherapy does not affect the patients’ participation in the trial. Palliative radiotherapy is permitted.

As no drug-drug interactions with ME are known, all drugs, except those mentioned in exclusion criteria, are allowed. Each drug given during study participation is regarded as concomitant medication and is registered in the electronic case report form (eCRF), including complementary compounds such as nutritional supplements, vitamins, natural remedies and homoeopathic drugs.

### Provisions for post-trial care {30}

Trial participants are covered by Swedish Pharmaceutical Insurance. Before study entry, potential participants are informed via the consent form that they will be offered post-trial treatment with ME for free.

### Outcomes {12}

Primary endpoint for the trial is OS defined as time from randomisation to death of any cause.

Secondary endpoints are HRQoL measured by the European Organisation for Research and Treatment of Cancer (EORTC) HRQoL questionnaires QLQ-C30 [54] and QLQ-PAN-26 [55] at study visits (baseline, 5–6 weeks, 2, 3, 4, 6 and 9 months after randomisation), body weight (documented weekly in patients’ study-specific diaries and at abovementioned study visits), corticosteroid use (continually from participants’ health records from baseline visit to end of study participation), adverse events (assessed at abovementioned study visits and continually from health records from baseline visit to end of study participation), costs for supportive care and costs for inpatient care (calculated from documentation in study-specific patient diaries and continually from health records from baseline visit to end of study participation).

OS as primary endpoint and HRQoL as secondary endpoints are chosen due to their high clinical relevance in pancreatic cancer patients, reflected by the fact that all palliative oncological treatment in this patient group aims to both improve HRQoL and to prolong survival, if possible.

Ancillary studies
Endpoints include analyses of blood cell count, differential, leukocyte subtypes, CRP, CA 19-9, albumin, anti-mistletoe lectin antibodies, IgG subtypes and cytokines at baseline and under follow-up. Whole blood is collected at baseline for isolation of DNA from peripheral leukocytes and subsequent analyses of DNA sequence and variations.The outcome of the qualitative study is to understand participants’ every-day life situations, symptom burden and management, self-administration of subcutaneous injections and experiences of participating in a randomised placebo-controlled trial on ME.

### Participant timeline {13}

The schedule of enrolment, interventions and assessments (Fig. 1) illustrates trial procedures from enrolment to end of study.

**Fig. 1 Fig1:**
[figure not shown]
Schedule of enrolment, interventions and assessments ^1^ Or as close to this date as possible ^2^ Phone call by study nurse ^3^ Three subcutaneous injections per week with placebo/ME; dose escalation from 0.01mg to 20mg ^4^ At screening visit: general condition, heart, lungs, abdomen and icterus (yes/no). At subsequent visits at least abdomen, icterus (yes/no) and general condition ^5^ Access is documented; referral if medical need for access ^6^ Recorded by participants in study-specific patient diary: n total parenteral nutrition infusions per week, n visits from palliative home care team per week, consumption of n dietitian-prescribed nutritional supplement drinks per day, injections, dosage, interruptions of study treatment, comments ^7^ Voluntary for participants at end of study

### Sample size {14}

Calculation of sample size was based on a number of considerations based on comparability with the randomised controlled trial on ME in advanced pancreatic cancer conducted in Serbia [36]. A basic assumption was that OS data from the control group in Serbia were comparable to OS data from Swedish patients not eligible for palliative chemotherapy. This assumption was supported by available quality assessments on survival in this type of patients undergoing palliative supportive care in Stockholm (unpublished data). Moreover, HR was estimated to be affected by longer OS for patients eligible for palliative chemotherapy due to better prognosis in general, expected higher proportion of participants in strata for palliative chemotherapy than in strata for best supportive care, potentially longer OS in control groups in both strata due to extensive palliative care [56] and expected longer time from diagnosis to trial inclusion than in Serbia. Finally, pragmatic reasons affecting feasibility (academic trial, comparatively rare type of cancer, trial duration) were considered.

A two-sided log rank test with an overall sample size of 290 patients (145 in the placebo group and 145 in the ME group) achieves 90% power at a 5% significance level to detect a hazard ratio of 0.67. In the placebo group, survival time in patients not eligible for palliative chemotherapy is expected to be shorter than for patients receiving palliative chemotherapy. However, the effect size for patients receiving ME compared to patients in the placebo group with respect to overall survival is expected to be the same in the two strata, i.e. a hazard ratio of 0.67.

Ancillary studies
Within the biomarker study, blood samples from at least 60 patients will be collectedWithin the qualitative study, approximately 30 participants from both the intervention and placebo groups will be interviewed

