### Methods for additional analyses (e.g. subgroup analyses) {20b}

Subgroup analyses will be performed regarding possible confounders such as prior and concurrent cytotoxic treatment, performance status and concomitant medication for symptom relief.

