## Discussion

Considering the pessimistic prognosis with short expected survival and considerable symptom burden for patients with advanced pancreatic cancer, there is an urgent need for more effective treatment options to prolong OS and improve HRQoL. It is of uttermost importance to find tolerable and potent therapies for the large proportion of newly diagnosed patients with advanced disease and frail performance status who currently have no treatment options other than best supportive care. Similarly, improved palliative treatments are necessary for patients with recurrent disease following curative intent treatments, as well as for patients with advanced disease and preserved performance status who are eligible for chemotherapy but have limited benefit from the latter. To our knowledge, this is the first placebo-controlled randomised trial assessing the impact of ME on OS and HRQoL in patients with advanced and/or relapsing pancreatic cancer. A previous randomised study from Serbia suggests that ME prolongs OS and increases HRQoL [35, 36], but the lack of placebo control and the exclusion of patients with palliative chemotherapy make generalisation difficult. The present trial was designed to overcome these limitations by adding a placebo group and including patients with and without chemotherapy. In the light of a recently established, international core set of patient-reported outcomes [62] such as global health status/QoL, physical ability, ability to work/do usual activities and abdominal complaints, our choice of secondary outcomes is highly clinically relevant. Moreover, the advanced integration of palliative care in the Swedish health care system [63] and the addition of two ancillary studies on biomarkers and qualitative interviews may contribute with other baseline data and in vivo effects of controlled ME, as compared to the study conducted in Serbia.

In the light of the increasing role of the immune system in oncological treatment development, it is essential to further investigate this relatively non-toxic immunomodulating therapy. As there is no previous connection of OS and HRQoL to immunological response, the biomarker study in a placebo-controlled double-blind setting may enable robust identification of ME-specific predictive biomarkers, as well as general prognostic biomarkers.

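### The chemotherapy subgroup should be defined by eligibility as randomised, not by concurrent cytotoxic treatment, which can change after randomisation

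*Protocol article*

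**What the plan says.** All references are to the protocol article.

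- **Subgroups** (Methods for additional analyses {20b}): "Subgroup analyses will be performed regarding possible confounders such as prior and concurrent cytotoxic treatment, performance status and concomitant medication for symptom relief".
- **Concomitant care** ({11d}): starting, ending or changing a line of palliative chemotherapy leaves a patient in the trial.
- **Randomisation** (Trial design {8}, Sequence generation {16a}): stratified by site and by eligibility for palliative chemotherapy (eligible or not).
- **Primary analysis** ({20a}): one ME:placebo hazard ratio from a log rank/Cox analysis stratified for centre and systemic oncological treatment.
- **Sample size** ({14}): 290 patients "achieves 90% power at a 5% significance level to detect a hazard ratio of 0.67". The rationale says that the "HR was estimated to be affected by longer OS for patients eligible for palliative chemotherapy due to better prognosis in general", and also by the "expected higher proportion of participants in strata for palliative chemotherapy than in strata for best supportive care". The next paragraph says that the effect of ME "is expected to be the same in the two strata, i.e. a hazard ratio of 0.67".
- **Evidence** (Background {6a}): the earlier randomised trial, in patients not eligible for chemotherapy, gave "HR = 0.49; 95% CI = 0.36–0.65". No survival hazard ratio is cited for patients on chemotherapy.
- **Aim** (Abstract, Discussion): ME is assessed on top of chemotherapy or best supportive care. Of the earlier trial the Discussion says that "the lack of placebo control and the exclusion of patients with palliative chemotherapy make generalisation difficult", and that this trial was designed to overcome those limits.

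**The concern.** Whether ME works alongside chemotherapy is one of the questions that this trial was set up to answer. The only subgroup named in the article that bears on it is cytotoxic treatment, prior and concurrent. The prior part is fixed before randomisation. The concurrent part is not.

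A patient must live long enough to start or change chemotherapy, and must be well enough to stay on it. The Background itself counts better tolerability of cytoreductive treatment among the best-supported effects of ME. If that is so, the patients classed as receiving chemotherapy may differ between the arms, and a hazard ratio within that group no longer compares like with like.

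Calling these variables confounders also misses the purpose. In a randomised comparison the question is whether the effect differs between groups, which calls for an interaction estimate.

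At stake is the reading of the result. One pooled hazard ratio could be taken as evidence of benefit on top of chemotherapy, supported only by a subgroup comparison that is open to bias, although the unbiased one is already in the database.

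**Working it through.** **1. The plan's own figure.** Inputs from Sample size {14}: two-sided alpha 0.05, power 0.90, hazard ratio 0.67, 1:1 allocation.

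- Schoenfeld: 4 × (1.960 + 1.2816)² / (ln 0.67)² = 4 × 10.508 / 0.1604 = 262.1, so 263 deaths.
- Freedman: (1.67/0.33)² × 10.508 = 25.61 × 10.508 = 269.1, so 270 deaths.

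263/290 = 91% and 270/290 = 93%. The article gives no event count, but 290 patients deliver 90% power if 91–93% have died by the analysis. The stated sample size is sound.

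**2. The two candidate subgroup variables.**

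| | Concurrent cytotoxic treatment {20b} | Eligibility {8}, {16a} |
|---|---|---|
| Fixed at randomisation | No, may start, stop or switch {11d} | Yes |
| Can depend on survival or on ME | Yes | No |
| Arms balanced by stratified randomisation | No | Yes |
| Named as a subgroup | Yes | No |

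**3. What estimates by randomised stratum would deliver.** The article says only that the chemotherapy stratum is expected to be the larger, so the split of deaths is an assumption, shown from 50/50 to 20/80. Total deaths are 263.

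- Expected 95% CI at a true 0.67: 0.67 × exp(±1.96 × 2/√d), with d the deaths in the stratum.
- What-if: the not-eligible hazard ratio is 0.49, as in the earlier trial, and the pooled value is 0.67. With w the not-eligible share of deaths, the eligible hazard ratio h solves w ln 0.49 + (1 − w) ln h = ln 0.67.
- Interaction power: Φ(|ln 0.49 − ln h| / √(4/d₁ + 4/d₂) − 1.96).

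| Not-eligible share | Deaths, not eligible / eligible | CI, not eligible | CI, eligible | h in the what-if | Interaction power |
|---|---|---|---|---|---|
| 50% | 132 / 132 | 0.48–0.94 | 0.48–0.94 | 0.92 | 72% |
| 40% | 105 / 158 | 0.46–0.98 | 0.49–0.92 | 0.83 | 54% |
| 30% | 79 / 184 | 0.43–1.04 | 0.50–0.89 | 0.77 | 38% |
| 20% | 53 / 210 | 0.39–1.15 | 0.51–0.88 | 0.72 | 24% |

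The 30% row in full: ln h = (−0.400 + 0.3 × 0.713)/0.7 = −0.266, so h = 0.77. The difference in logs is 0.713 − 0.266 = 0.447, its standard error √(4/79 + 4/184) = 0.269, and Φ(0.447/0.269 − 1.96) = Φ(−0.30) = 38%.

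**4. The wording of the rationale.** If the hazard ratio is the same in both strata, the mix of strata cannot move a stratified hazard ratio, and longer control survival alone does not move it under proportional hazards. Mixing does dilute an unstratified hazard ratio. With exponential survival, control medians of 2.7 months (the earlier trial's control group) and an assumed 5–11 months on chemotherapy, and a chemotherapy share of 50–80%, a common 0.49 becomes 0.50–0.58. That does not reach 0.67. So either the effect is taken to differ between strata, or 0.67 rests on the other reasons listed and the mix argument adds little.

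**The case against.** - **The list is open and the analysis plan is not shown.** The subgroup list gives examples only, and the article defers detail to a separate analysis plan. Estimates by stratum and interaction tests are commonly specified there, so their absence from the article is no finding. This stands. What remains is the variable that the article does name, which is a poor one if followed as written.
- **The variables are close.** Section {20a} describes the stratum in terms of systemic treatment, so concurrent might have been meant as treatment at entry. That is possible. The text does not say so, and {11d} makes the difference matter.
- **The 0.67 has other supports.** Sample size {14} also cites extensive palliative care in both strata, longer time from diagnosis to inclusion, and feasibility. This stands. No derivation of 0.67 is shown, so a reader might infer that it was computed from the stratum mix, but the article does not establish that.
- **The gain is modest.** Also true. The intervals in the 30% row overlap heavily, and the interaction test is weak unless the effects differ greatly.
- **The pooled hazard ratio answers the stated primary objective.** Agreed. The stratified test remains a valid test of no effect.

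**Conclusion.** The concern holds as a point about how a planned subgroup is defined. Built on concurrent cytotoxic treatment, it can be shaped by survival and by ME, while the clean randomised factor goes unnamed. The point matters because the equal-effect assumption has no cited survival hazard ratio behind it for patients on chemotherapy.

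A reader might go further and infer that the pooled result describes neither type of patient. The documents do not show that. It would follow only if the effects differed, for example if the earlier trial's 0.49 held in not-eligible patients, whereas the plan expects 0.67 there. Nor do they support a claim that the sample size is wrong: N = 290, alpha, power and the pooled stratified primary test are unaffected.

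The inconsistency in Sample size {14} is a secondary matter of wording. The precision figures assume 263 deaths and splits that the article does not give.

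**What to change.** 1. In {20b}, define the chemotherapy subgroup by eligibility for palliative chemotherapy as randomised. Report the ME:placebo hazard ratio with 95% CI in each stratum and one treatment-by-stratum interaction estimate with its CI. Present these as supportive estimates of effect modification, labelled imprecise, especially for patients not eligible. Any analysis by chemotherapy actually received should be marked as exploratory and not a randomised comparison.
2. In {14}, either call 0.67 an assumed average and state the expected mix, or justify a common 0.67 without the mix argument.

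The cost is wording in the protocol and analysis plan, agreed before unblinding, and one analysis on data already collected. No extra patients are needed. The drawback is that wide stratum intervals may be over-read, hence the label.
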